## Management of preeclampsia

Prevention of preeclampsia remains contentious and is an area of active research, particularly the use of anti-inflammatory and micronutrients in pregnancy. The anti-platelet agents like aspirin have be shown to reduce the risk of preeclampsia by 17% [[7](#_ENREF_7)]. On the other hand, calcium supplementation during pregnancy is shown to halve the risk of preeclampsia, but only in women with low dietary intake of calcium [[8](#_ENREF_8)].

The definitive treatment of preeclampsia is the delivery of the fetus and placenta. However, before and after delivery of the baby and placenta, the goal of management is to control the blood pressure to normal range and minimize the development of complications like eclampsia. The choice of anti-hypertensive to use for control of raised blood pressure is guided by the respective national guidelines and there are variety of antihypertensive drugs which are safe in pregnancy. For prevention and control of eclampsia, magnesium sulphate is the drug of choice[[3](#_ENREF_3)]. It has be shown to reduce the risk of eclampsia by over 50% [[9-11](#_ENREF_9)].

## Administration of magnesium sulphate

In the management of preeclampsia and eclampsia, magnesium sulphate therapy could be given by continuous IV infusion or by administering an IV bolus and IM doses for the loading dose followed by IM injections every 4 hours. The IV regimen was described by Zuspan, whereby a loading dose of 4 gm of Magnesium sulphate IV over 10-15 minutes is followed by an infusion of 1 gm/hour continued for 24 hours after the last seizure [[12](#_ENREF_12)]. In most health facilities especially in low resource settings, the rate of infusion is controlled manually. However, in high resource settings, the IV infusion is administered by a variety of programmable electronic pumps. These electronic pumps are expensive and require electricity or battery to run it, making it less appropriate in low resource settings. In low resource settings due to unavailability of the electronic pumps, the alternative regimen described by Pritchard is used [[13](#_ENREF_13)]. The Pritchard regimen involves administration of loading dose of 4 gm of 20% magnesium sulphate IV over 10-15 minutes, immediately followed by 10 gm of 50% magnesium sulphate IM (5gm on each buttock). The maintenance dose of 5 gm of 50% magnesium sulphate IM every 4 hourly in alternate buttocks continued for 24 hours after the last convulsion or delivery of the fetus, whichever is later. The IM injections are associated with pain, hot flushes, somnolence and abscess formation at the site of injection. A number of guidelines have recommended the addition of 1 ml of lignocaine to the IM solution to alleviate the pain. Other adverse events associated with magnesium sulphate are reduced patellar reflex, respiratory depression and oliguria. The concerns about the toxicity of magnesium sulphate has been reported to result in reluctance of some of the health professionals to administer it without the availability of antidote (Calcium gluconate). However a review by Smith et al point out that the incidence of severe side effects is very low[[14](#_ENREF_14)].

## Springfusor and flow control tube

The Springfusor and Flow Control Tube (FCT) are developed by Go Medical Industries Pty Ltd based in Australia [[15](#_ENREF_15)]. The Springfusor pump and FCT is intended to provide constant IV or subcutaneous (SC) infusions in either 10ml, 30ml or 50ml configuration at a variety of preset flow rates.

[figure not shown]
The Springfusor (Fig. 1) is powered by the potential energy stored within a spring at the heart of the device. The spring is compressed by the action of loading the Springfusor with the compatible syringe and FCT. The spring provides a constant force to the barrel of the loaded syringe. The flow rate is controlled by the FCT which offers consistent resistance to produce a steady flow. The FCT is a fine bore tube designed to provide a metered constant flow for IV infusion. FCTs has easy fitting to the patients cannula. The FCT exist in a variety of flow rates which enables the user to attain the desired output for exact IV delivery needs. While the Springfusor can be reused indefinitely on different patients, the FCT must be replaced after each use.

The Springfusor syringe infusion pump is a low cost, non-sterile, reusable pump that requires no external power source. It is simple to use and setup, and requires only minimal training to load and operate. It is lightweight, portable and therefore does not limit the mobility of the patient.

The Springfusor has been used to administer magnesium sulphate in the treatment of severe preeclampsia in India [[16](#_ENREF_16)]. In this trial, Mundle and colleagues compared the manually administered IV loading dose followed by maintenance therapy given by IM route of administration via a syringe, to a loading dose and maintenance therapy given through IV infusion administered by a Springfusor device. Though there were no difference in maternal and neonatal morbidity, the Springfusor had few side effects. Earlier in 1994, Freebairn et al in Australia compared the Spingfusor infusion device to intermittent bolus on administration of muscle relaxant. They were able to show that Springfusor provided a more constant level of paralysis compared to intermittent bolus administration [[17](#_ENREF_17)].

# Statement of the problem

Different anticonvulsants have been used for the prevention and treatment of seizures in preeclampsia and eclampsia, and they include; magnesium sulfate, phenytoin, diazepam, and “lytic cocktail” (usually chlorpromazine, promethazine, and pethidine). World health organization recommends magnesium sulphate as the anticonvulsive drug of choice for the treatment of severe preeclampsia and eclampsia [[3](#_ENREF_3)]. Magnesium sulphate is administered parenterally by intravenous (IV) and or intramuscular (IM) routes. The intravenous therapy is commonly administered following the Zuspan regimen that requires an initial loading dose of 4 gm of magnesium sulphate over 15-20 minutes, followed by 1-2 gm hourly maintenance dose continuing for 24 hours after the loading dose or the last eclamptic fit [[12](#_ENREF_12)]. This therapy is best delivered by infusion pumps. In most of the low resource settings magnesium sulphate administration follows the Pritchard regimen. The regimen is particularly complex and requires both the IV and IM administration. The loading dose of 4 gm is often delivered using an IV-push in which clinicians slowly inject magnesium sulphate with a syringe over 15-20 minutes. This is immediately followed by IM injection of 10 gm of magnesium sulphate into the gluteal muscles (5 gm on each buttock). The maintenance dose of 5 gm IM injection every 4 hourly for 24 hours. The Pritchard regimen requires different dilutions for IV and IM doses, and different doses for IV, IM, loading, and maintenance doses. This regimen requires a 20% dilution of magnesium sulphate for the IV loading dose, which necessitates the health providers to calculate the quantity of sterile water to add to the magnesium sulphate solution. In most settings, health providers do not encounter eclampsia very often; and when they do, trying to remember the complex regimen is challenging. In addition the Pritchard regimen requires administration of large, painful intramuscular (IM) injections (11 mL) every 4 hours for maintenance doses. The repeated IM injections can lead to risk for and development of abscess. Because of pain associated with the injection, some providers do not administer maintenance therapy and patients too, may discontinue the maintenance dose for the same reason. In addition the slow IV-push loading dose leads to inconsistent flow rates and is time-consuming, in setting with staff shortages. Furthermore, if magnesium toxicity occurs with IM regimen, the IM dose may not be reversed. The fear that toxicity may occur might lead providers to undertreat with magnesium sulphate. In the circumstances that low resources settings cannot afford electronic infusion pumps, there is a need to test alternative devices that can effectively deliver magnesium sulphate and safely, at cheaper cost, and acceptable to the patient and health provider. The Springfusor pump designed by Go Medical Industries is a promising alternative to Pritchard regimen and is designed to simplify continuous IV infusions. The Springfusor pump does not require electricity and its reusable. The aim of this study is to assess the acceptability and safety of Springfusor pump in delivery of magnesium sulphate for the treatment of preeclampsia and eclampsia.

## Justification

Preeclampsia and eclampsia (PE/E) are life-threatening for both the mother and the fetus. Ministry of Health guidelines recommends magnesium sulphate using Pritchard regimen for the prevention and control of seizures. Given the unavailability of electronic infusion pumps in low resource settings, and with the limitations of Pritchard regimen Springfusor pump is hoped to be an alternative infusion pump. It is cheaper than electronic infusion pumps, reusable and does not restrict the patient’s mobility. It can used in setting without electricity. In addition this pump could reduce the side effects associated with IM injections eg, pain, hot flushes and abscess formation. It is hoped that the Springfusor may improve the acceptability and continuation rate of magnesium sulphate dosing. The findings from this study will help determine if a Springfusor device can facilitate ease and safety of MgSO4 administration. If the Springfusor device is advantageous, then the results from this study can be used to argue for scale-up of this product, to ultimately expand access to prevention and control of seizures in women with preeclampsia. The results from this project will help the Ministry of Health to improve the care of women who experience high blood pressure during pregnancy. We hope that the Springfusor could be of benefit to women with high blood pressure who are to receive magnesium sulphate in that you have less side effects

## Research questions

1. Acceptability:
   1. What is the overall acceptability of Springfusor use among women with preeclampsia and eclampsia?
   2. What is the acceptability of the springfusor use for magnesium sulphate administration among health providers
   3. What is the level of pain associated with using Springfusor compared to the standard of care in administration of magnesium sulphate?
2. Effectiveness of Springfusor:
   1. What is the discontinuation rate of magnesium sulphate administration using a Springfusor pump compared to standard of care?
3. Safety
   1. What is rate of complications in the two arms?

Hypothesis

Use of Springfusor pump in the administration of magnesium sulphate in women admitted with preeclampsia and eclampsia is more acceptable than the hospital standard practice

Objectives

Primary objective

1. To compare the acceptability of the Springfusor pump to the standard of care in the administration of magnesium sulphate.

Secondary objective

1. To compare the proportion of complications between the Springfusor pump and the standard of care groups
2. To determine level of pain associated with using Springfusor compared to the standard of care?
3. To determine the discontinuation rate of administration of magnesium sulphate among women admitted with preeclampsia and eclampsia
4. To assess the reliability of Springfusor pump in the delivery of magnesium sulphate when used repeatedly
5. To assess the acceptability of the Springfusor pump for the administration of magnesium sulphate among the health providers.

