- *Feasibility of Springfusor pump use: ⃰* The proportion of women who have a Springfusor used for administration of magnesium sulphate and experience some technical problem with its use, blockage of FCT, the number of attempts made prior to successful Springfusor placement, the number of failed Springfusor placement and the number of FCTs and spilled magnesium sulphate used will also be documented.
- The *reliability** of the Springfusor to administer magnesium sulphate in the prescribed time will assessed for the loading period and the maintenance period. The intra-correlation coefficient for the device will be calculated.

These outcomes will be compared between the women in the two arms. A *outcome will be reported only for women who will have magnesium sulphate administered using Springfusor

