**Data analysis**

Data analysis will be performed by the PI. Descriptive statistics will be used to summarize baseline characteristics of study participants and assess if randomization was successful. The baseline characteristics will too give guidance as to which variables need to be adjusted for in the final analysis.

Acceptability and safety data will be evaluated using intention-to-treat (ITT) analysis. For comparing the maternal health outcome between intervention and control arms, the main analyses will look at the following variables;

1. Proportion of study participants who regarded magnesium sulphate administration using Springfusor or Pritchard route was acceptable. This will be compared using chi-square.
2. *Rate of complications of preeclampsia and its management:* Proportion of preeclamptic and eclamptic women who developed magnesium sulphate toxicity, abnormal liver and renal function test, infection at the injection and maternal deaths
3. The intensity of pain will be analysed using a ttest and presented as means and standard deviation
4. *Feasibility of Springfusor pump use:* The proportion of women who have a Springfusor used for the administration of magnesium sulphate and experience some technical problem with its use, blockage of FCT, the number of attempts made prior to successful Springfusor placement, the number of failed Springfusor placement and the number of FCTs used and spilled magnesium sulphate.
5. *The reliability of the springfusor:* The intra-class correlation coefficient (ICC) will be calculated. The closer the ICC to 1, the higher the reliability, ICC <0.4; the poor the reliability and ICC 0.4-0.75; the fair the reliability.

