# Safety and monitoring

The following mechanisms will be employed to ensure the data quality and integrity of the study. An independent data and safety monitoring board (DSMB) will be established to review the data and make recommendations to investigators concerning study continuation and study modification. The main purpose of the DSMB is to ensure that the study participants are not exposed to undue risk. The DMSB will be called upon to review reported serious adverse events and provide advice on management of the study with relation to risk, and will help assure the continued scientific validity and merit of the study. An interim analysis will be conducted in the study when 2/3 of participants have been recruited. Based on the analysis and if deemed necessary, the DSMB will be asked to provide recommendations on study modification. All data analyzed by the DSMB will be reviewed in strict confidence.

The DSMB will consist of three professionals whose combined experience covers the fields of obstetrics and gynaecology, preeclampsia and eclampsia, biostatistics, and ethical conduct of human subject research. Qualifications for selection include: 1) Expertise in the fields of interest, 2) Experience in conduct of clinical trials and statistical knowledge, 3) independence from the direct management of the clinical trial, 4) no financial, scientific or other conflict of interest. Signed conflict of interest statements from each board member must be on the file at PI office prior to initiating DSMB activities.

Accountability log will be used to track the use of Springfusor devices and FCTs during the study. The product will be stored in accordance with the requirements of Springfusor. Any unused Springfusor and FCTs will be held at Mulago Hospital until final instructions are received from Go Medical Ltd.

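### Secondary objective 4 asks about pump reliability on repeated use, but the only analysis fixed, a graded ICC, shows neither change with use number nor deviation from the prescribed time

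*Protocol*

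**What the plan says.** The Objectives (under Research questions) list as secondary objective 4: "To assess the reliability of Springfusor pump in the delivery of magnesium sulphate when used repeatedly".

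Outcome Measures gives the matching outcome as the reliability "of the Springfusor to administer magnesium sulphate in the prescribed time will assessed for the loading period and the maintenance period", and adds: "The intra-correlation coefficient for the device will be calculated". It is marked as an outcome reported only for women treated with the Springfusor.

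Data analysis, item 5, says "The intra-class correlation coefficient (ICC) will be calculated" and grades it: values nearer 1 are better, with "ICC <0.4; the poor the reliability and ICC 0.4-0.75; the fair the reliability". The ICC form, the class (pump or woman) and the repeated factor are not named. No analysis by use number and no comparison of early with late uses is named.

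On the device, the literature review section on the Springfusor and flow control tube (FCT) states "While the Springfusor can be reused indefinitely on different patients, the FCT must be replaced after each use" and "The flow rate is controlled by the FCT which offers consistent resistance to produce a steady flow".

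On records, Study procedure has the loading dose timed, and each Springfusor maintenance syringe timed by stop clock. Data handling describes one case record form per participant. Safety and monitoring adds: "Accountability log will be used to track the use of Springfusor devices and FCTs during the study". The protocol does not say that pump ID or use number is entered with the infusion time.

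**The concern.** The objective concerns performance under reuse, and its outcome is timing against a prescribed duration. An ICC is a share of variance: how much of the spread in infusion times lies between classes rather than within them. It estimates neither a change over successive uses nor a distance from a target. A pump whose late infusions run long can receive the same grade as one that holds its time.

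Reusability is one of the protocol's reasons for proposing the pump, and the Justification hopes that the results will support scale-up. Objective 4 is the only objective that addresses performance on reuse. The data-capture side is also time-critical: if pump ID and use number are not recorded while the trial runs, no later analysis plan can recover them.

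**Working it through.** **Stated figure.** The protocol gives no target, precision or sample size for objective 4, only the ICC cut-offs, so there is no figure to reproduce. The number of pumps, the standard deviations and the size of any drift are not given. The values below are assumptions and serve as illustration.

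**1. One-way ICC by pump and the order of uses.** With m uses per pump,

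ICC = (MSB − MSW) / (MSB + (m − 1) MSW).

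MSB depends on the pump means and MSW on the within-pump variances. Reordering a pump's uses changes neither. This is algebra and needs no assumed values. Shuffling the uses within pumps left the ICC unchanged in every simulated run.

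**2. What a drift does to this ICC.** A linear drift of total size d over a pump's life adds about d²/12 to the within-pump variance, so

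ICC ≈ σ²(pump) / (σ²(pump) + σ²(within) + d²/12).

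Assume 20 pumps and a 240-minute infusion. The 28 g total in Intervention is 4 + 6 × 4, so six maintenance uses per woman, and 241 × 6 / 20 ≈ 72 uses per pump. Take a pump SD of 10 min and a within-pump SD (mainly tube) of 12 min.

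| Case | Approximation | Simulated mean ICC |
|---|---|---|
| No drift | 100/(100+144) = 0.41 | 0.40 |
| 24-min drift | 100/(100+144+48) = 0.34 | 0.34 |
| 48-min drift | 100/(100+144+192) = 0.23 | 0.22 |
| No drift, noisier tubes (SD 13.9) | 100/(100+192) = 0.34 | 0.33 |

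A 24-minute drift and somewhat noisier tubes give nearly the same ICC, so a low value cannot be traced to reuse.

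**3. Two-way ICC.** Suppose use number is the second factor. The consistency form takes the shared use-number effect out. With 10 pumps, 150 uses each, and between- and within-pump SDs of 5%, it stays at about 0.475 for drifts of 0%, 10% and 20%. The absolute-agreement form puts the drift variance in the denominator, so it falls as in step 2 and still reports no trend.

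**4. Woman as class.** The class is unnamed, so this is also open. With six uses per woman, pump SD 5 min, within SD 12 min and drift across successive women, the mean ICC is 0.14, 0.36, 0.64 and 0.87 for drifts of 0, 24, 48 and 96 min. Here a drifting pump would be graded as more reliable.

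**5. The prescribed time.** Adding 60 minutes to every infusion in one simulated data set left the ICC at 0.296. A constant shift cancels from every mean square.

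**6. What the same data could show.** Regress infusion time on use number within pump, scaled 0 to 1 over the pump's life. In the setting of step 2 there are 20 × 72 = 1,440 infusions, and the slope has SE ≈ 12 / √(1,440/12) = 12/10.95 ≈ 1.1 min. A 5-minute drift is then about 4.6 standard errors. In simulation the slope test rejected in about 99% of runs at 5 min and in all runs at 10 min or more, with about 5% false positives. The mean ICC was 0.40 both without drift and with the 5-minute drift. The drift was assumed common to all pumps.

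**The case against.** The strongest reply is that "To assess the reliability of Springfusor pump in the delivery of magnesium sulphate when used repeatedly" may mean repeat-to-repeat consistency, which is what an ICC addresses. The protocol never mentions wear, ageing or drift. That stands: spring wear is only one reading. On the consistency reading, though, the ICC still says nothing about the prescribed time, which is how Outcome Measures defines reliability.

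A second reply is that the ICC form is open and may be settled in a statistical analysis plan that is not shown, and that a two-way ICC does respond to order. With 10 pumps, 150 uses and a 20% drift, the consistency form is about 0.48 in true order and about 0.28 after shuffling. That is correct, but 0.48 is also its value without drift, so it does not report the change either.

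A reader might infer three stronger points that the documents do not support:

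- **That the trial cannot detect a change with reuse.** The infusions are timed and devices and tubes are logged. The limit lies in the named analysis and the unstated link between the records. The layouts of the form and log are not shown, so a pump-number field may exist.
- **That a new tube at each use hides a trend.** It adds noise to each time, and that noise is already in the within-pump SD of step 6. Confounding would need tube batches to change in step with pump age, which nothing in the protocol suggests.
- **That the plan would label a worn pump reliable.** With 5% SDs, the mean one-way ICC is 0.47 without drift and 0.40 with a 10% drift, while mean time rises from 241 min (first 15 uses) to 263 min (last 15). Both means fall in the fair band, but 0.40 lies on its edge and 46% to 48% of runs fall below it. At 20% drift the mean is 0.29, which is graded poor. With a between-pump SD of 3%, the mean is about 0.26 without drift and 0.21 with 10%, poor either way. Fair is also not the same as reliable.

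**Conclusion.** The point holds for the planned analysis. A graded ICC cannot show a change in delivery with the number of uses, and it does not measure deviation from the prescribed time. The order result for the one-way form and the shift result are algebraic and hold whatever the variances. The simulated ICC values and the 99% detection figure rest on assumed pump numbers, SDs and linear drifts, and should be read as illustration.

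This is not merely detail left to a later plan. The protocol itself names the statistic and its cut-offs, and these do not match its own objective and outcome definition.

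Severity is minor. The outcome is secondary and reported in the Springfusor arm only. The acceptability comparison, the safety outcomes, discontinuation and the sample size are unaffected.

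**What to change.** 1. **Data capture (Study procedure; Safety and monitoring).** Record pump ID and cumulative use number, and tube lot if available, with each timed infusion, so that the device log and the case record form can be linked.
2. **Analysis (Data analysis, item 5).** Report infusion time as a ratio to the prescribed time, separately for loading and maintenance. Estimate its change by use number within pump, with a 95% CI, from a mixed model with random effects for pump and woman. Add a tube-lot term if the lot is recorded.
3. **ICC.** Use the above alongside or in place of the graded ICC. If the ICC stays, name its form and class, and describe it as a measure of consistency only.

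The cost is two or three fields per infusion and one model, with no added patients or procedures. The fields have to be in place while infusions are being timed.
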